## Abstract

**Background:**

Coronary microvascular disease (CMVD) is a major cause of angina in patients with ischemia and nonobstructive coronary arteries (INOCA) syndrome. It is characterized by an imbalance between myocardial oxygen supply and demand, leading to reduced exercise tolerance and impaired quality of life. Because of heterogeneous diagnostic approaches and the lack of disease-modifying therapies, CMVD remains underdiagnosed and undertreated. Shexiang Tongxin Dropping Pill (STDP), a traditional Chinese medicine formulation, has shown protective effects on the coronary microvasculature in preclinical and preliminary clinical studies. However, high-quality randomized evidence and objective functional validation are still lacking. This study therefore aims to evaluate the efficacy and safety of STDP in patients with CMVD using cardiopulmonary exercise testing (CPET) as the primary functional outcome and to develop an artificial intelligence (AI)-assisted myocardial contrast echocardiography (MCE) tool to improve CMVD detection and subgroup classification.

**Design:**

This is a prospective, multicenter, randomized, double-blind, placebo-controlled clinical trial with a nested diagnostic design. CMVD will be diagnosed by stress MCE, and eligibility will require evidence of reduced myocardial perfusion or perfusion defects. Eligible patients with CMVD will be randomized at a 1:1 ratio to receive STDP or a matched placebo for 12 weeks. The primary endpoint is the change in peak oxygen uptake (peak VO₂) measured by cardiopulmonary exercise testing (CPET). The secondary outcomes include other CPET indices, angina severity, quality of life, and circulating biomarkers. The nested diagnostic study uses retrospectively and prospectively collected MCE datasets to develop AI-based models for automated myocardial segmentation, perfusion curve analysis, and CMVD classification, with performance assessed against established reference standards.

**Discussion:**

By combining quantitative microvascular imaging, functional exercise assessment, and AI-assisted diagnostics in a single protocol, this study proposes a therapeutic-diagnostic framework for CMVD. This study is expected to provide high-quality randomized evidence for the use of STDP in CMVD and to offer a scalable and objective approach to improve diagnosis, risk stratification, and individualized management in patients with functional coronary ischemia.

**Clinical Trial registration:**

http://itmctr.ccebtcm.org.cn/, International Traditional Medicine Clinical Trial Registry (ITMCTR), TMCTR2025000414.

## Introduction

Coronary microvascular disease (CMVD) is increasingly recognized as a major mechanism of ischemia with nonobstructive coronary arteries (INOCA) (1). CMVD is defined as structural and/or functional abnormalities of the coronary microcirculation that impair myocardial perfusion and lead to recurrent angina, reduced exercise tolerance, and poorer quality of life. CMVD is common in women, people with diabetes, and patients with cardiac syndrome X (2). Its prevalence is difficult to determine because diagnostic pathways vary and functional testing is not standardized. Among patients evaluated for angina, 40%–70% have no obstructive epicardial coronary disease, and approximately 20%–30% of this subgroup meets the diagnostic criteria for CMVD (3). Current guideline-directed care focuses on antianginal therapy and risk factor control (1). These approaches may improve symptoms in some patients, but they do not directly address the underlying microvascular pathology. As a result, recurrent symptoms, limited functional capacity, and residual cardiovascular risk often remain.

Noninvasive imaging and functional assessment may help address these diagnostic and treatment gaps. Stress myocardial contrast echocardiography (MCE) allows real-time quantitative assessment of myocardial microvascular perfusion and provides hemodynamic information related to ischemic physiology (4). Stress MCE yields the stress‒to‒rest myocardial blood flow (MBF) ratio, termed the myocardial blood flow reserve (MBFR), which is a validated index of microvascular vasodilatory capacity (5). When obstructive epicardial coronary disease has been excluded, MBFR is functionally comparable to coronary flow reserve (CFR). Compared with radionuclide imaging and cardiac magnetic resonance, MCE can be performed at the bedside, does not involve ionizing radiation, can be repeated, and is relatively cost-effective. These features support its use in longitudinal evaluation in multicenter studies (6, 7). Along with perfusion imaging, cardiopulmonary exercise testing (CPET) provides an objective and integrated assessment of functional capacity, gas exchange, and overall cardiopulmonary performance (8). In CMVD, impaired microvascular perfusion limits the ability to match myocardial oxygen delivery to metabolic demand during exercise, which contributes to exercise intolerance. CPET captures this limitation through peak oxygen uptake (peak VO_2_), a robust and prognostically relevant measure that links symptoms to physiological impairment and helps distinguish cardiac from noncardiac causes of exercise limitation (9).

Recent advances in artificial intelligence (AI) offer tools for automated myocardial segmentation, kinetic modeling of perfusion curves, and pattern recognition. In this study, AI-assisted analysis will be applied to assess its impact on interobserver variability, detection of subtle perfusion abnormalities, and standardization of perfusion classification. This approach is designed to enhance MCE-based workflows and facilitate standardized analysis for CMVD evaluation.

Shexiang Tongxin Dropping Pill (STDP; National Medical Products Administration approval No. Z20080018) is a proprietary Chinese medicine derived from the classical prescription Zhibaodan and formulated according to the aromatic-warming principle for coronary artery disease. Standardized quality control procedures and chemical fingerprinting have been established (10). Preclinical studies suggest that STDP has anti-inflammatory, endothelial-protective, and cardioprotective effects, partly by reducing macrophage-mediated inflammation, vascular dysfunction, and microvascular obstruction after ischemia–reperfusion injury (11, 12). In clinical settings, preliminary benefits have been reported in patients with coronary slow flow (13). However, its efficacy in nonobstructive coronary artery disease and CMVD remains uncertain because adequately powered and rigorously designed randomized controlled trials with objective physiological and functional endpoints are limited.

Therefore, we designed the STDP-CMVD trial, a hybrid therapeutic-diagnostic study. This study includes a multicenter randomized controlled trial to evaluate the efficacy and safety of STDP and a nested diagnostic study that uses MCE-derived datasets to develop and validate an AI-assisted automated tool for CMVD detection and stratification.

## Study design, methods and analyses

### Study design

This is a multicenter, randomized, double-blind, placebo-controlled trial designed to evaluate the efficacy and safety of STDP in patients with CMVD. The diagnosis of CMVD is confirmed by stress MCE during the screening period, with eligibility requiring evidence of reduced myocardial perfusion or perfusion defects (CFR <2.0). After providing written informed consent, eligible participants will be randomized at a 1:1 ratio to receive STDP or a matched placebo in addition to guideline-directed standard therapy for 12 weeks. The study included a screening period of up to 1 week, a 12-week treatment period, and end-of-treatment assessments. The primary endpoint is the change in exercise capacity measured by the peak VO₂ on the CPET. The secondary endpoints include additional CPET indices, angina burden, psychological status, health-related quality of life, and circulating biomarkers. The overall study flowchart is shown in Figure 1.

**Figure 1 F1:**
[figure not shown]
Study design of the STDP-CMVD randomized controlled trial integrating functional and imaging-based assessments. CMVD, coronary microvascular disease; MCE, myocardial contrast echocardiography; CFR, coronary flow reserve; CPET, cardiopulmonary exercise testing.

The study was approved by the Ethics Committee of Guangdong Provincial Hospital of Chinese Medicine (No. BF-2024-250-01). The protocol follows the SPIRIT recommendations, will be conducted in accordance with Good Clinical Practice (GCP), and will be reported in line with the CONSORT. During the study, any protocol changes that may affect study conduct, participant safety, or scientific integrity will be submitted as amendments and approved by the ethics committees at all participating sites before implementation.

### Recruitment

#### Recruitment and study setting

Participants will be screened and enrolled from cardiology departments or chest pain clinics in tertiary hospitals in Beijing and Guangdong Province, including Guangdong Provincial Hospital of Traditional Chinese Medicine (Guangzhou), China–Japan Friendship Hospital (Beijing), Guangdong Provincial People's Hospital (Guangzhou), Nanfang Hospital of Southern Medical University (Guangzhou), Dongguan Hospital of Guangzhou University of Chinese Medicine (Dongguan), and Zhongshan Hospital of Traditional Chinese Medicine (Zhongshan). This setting will allow the recruitment of a demographically diverse population from both northern and southern China. Recruitment will be conducted through investigator referrals and public advertisements, including online platforms and offline posters or flyers placed in outpatient areas, hospital bulletin boards, and community settings.

During prescreening, trained research staff will provide standardized information regarding study objectives, procedures, anticipated benefits, and potential risks. Interested individuals will then undergo clinical evaluation and diagnostic assessment. Eligibility will be assessed independently by two senior physicians with at least 5 years of clinical experience. Eligible candidates who provide written informed consent will be enrolled and randomized via a centralized, web-based randomization system. For individuals who fail screening, basic demographic information and reasons for ineligibility will be recorded. The planned recruitment period is February 28, 2025, to December 31, 2027.

#### Diagnostic criteria

CMVD will be diagnosed according to the Integrated TCM–Western Medicine Guidelines for CMVD (14), with a focus on the microvascular angina (MVA) phenotype. The participants must satisfy all four domains:
Symptoms suggestive of myocardial ischemia:
(a)Typical angina (exertional or at rest), or(b)Atypical ischemic equivalents (e.g., dyspnea, interscapular pain).Exclusion of obstructive epicardial coronary artery disease (CAD): Coronary CTA or invasive angiography demonstrating <50% diameter stenosis or stenosis ≥50% and ≤75% with fractional flow reserve (FFR) or quantitative flow ratio (qFR) > 0.80.Objective evidence of myocardial ischemia (≥1 of the following):
(a)Ischemic ECG changes during spontaneous chest pain episodes;(b)stress-induced chest pain and/or ischemic electrocardiographic changes, with or without wall motion abnormalities and/or perfusion defects.MCE revealed reduced myocardial perfusion or perfusion defects.

#### Inclusion criteria

Participants will be eligible if all of the following are met:
CMVD was diagnosed according to the above criteria;Angina episodes ≥2 times per week;Age 18–80 years;Willingness and ability to complete the study procedures and follow-up, with written informed consent.

#### Exclusion criteria

Participants will be excluded if any of the following apply:
Known hypersensitivity to STDP or its components;Noncardiac causes of chest pain (e.g., gastrointestinal or musculoskeletal);Persistent severe angina (Canadian Cardiovascular Society (CCS) class IV);ST-segment depression was marked with routine activity;Left ventricular ejection fraction (LVEF) <30%, refractory heart failure, or cardiogenic shock;Planned coronary artery bypass grafting (CABG) or percutaneous coronary intervention (PCI) during the study period;Epicardial coronary spasm documented by acetylcholine testing, angiographic spasm, or typical vasospastic features judged clinically;Conditions that may affect CPET interpretation or increase risk, such as chronic obstructive pulmonary disease, poorly controlled asthma, interstitial lung disease, pulmonary embolism, or severe anemia;eGFR <30 mL/min/1.73 m^2^;Significant hepatic disease or ALT/AST >3× upper limit of normal;Serious comorbidities (e.g., malignancy) likely limit survival/adherence;Uncontrolled severe hypertension or clinically significant arrhythmias;Participation in another clinical trial within 30 days or prior to randomization;Pregnant or planned pregnancies during the study period;Any condition judged by investigators to compromise safety or adherence;Severe valvular heart disease or cardiomyopathy;Known allergies to ultrasound contrast agents;Absolute contraindication to pharmacologic stress, such as regadenoson or adenosine.

### Sample size estimation

The primary efficacy endpoint is the change in peak VO₂ after 12 weeks of treatment. The sample size estimation was based on data from the iPOWER study (15), in which the CFVR served as the diagnostic criterion for coronary microvascular dysfunction (CMD). In participants with a CFVR ≥2.0 (non-CMD group, *n* = 22), the median peak VO₂ was 28.6 mL/kg/min (IQR: 22.1–31.7); in those with a CFVR <2.0 (CMD group, *n* = 27), the median peak VO_2_ was 17.3 mL/kg/min (IQR: 15.5–21.3). On the basis of these data, the estimated between-group difference in means was 4.71 mL/kg/min, with a pooled standard deviation of 6.5 mL/kg/min. Using a two-sided superiority design with a significance level *α* = 0.05 and a target power of 90% (1-*β* = 0.90), the required evaluable sample size per group was calculated using the formula for two-independent-sample *t*-test with equal variances:$$n=2\times {\left(\frac{Z_{1-\alpha /2}+Z_{1-\beta }}{\Delta /\sigma }\right)}^{2}$$Where $\;Z_{1-\alpha /2}$ = 1.96, $Z_{1-\beta }$  = 1.282, and *δ* = 4.71, *σ* = 6.5. This given *n* = 41.5 per group, rounded up to 42 evaluable subjects per group (total 84). The calculation was performed using PASS 2023 (NCSS, LLC, Kaysville, UT, USA), which confirmed that 42 subjects per group achieve 90.68% power under the same assumptions.

To account for an anticipated 15% attrition rate (dropout or loss to follow-up), the sample size was inflated using the formula:$$n^{\prime }=\frac{n}{1\text{-}\mathrm{DR}}$$where DR is the dropout rate. With *n* = 42 and *DR* = 0.15, *n'*=42/0.85 = 49.41, rounded up to 50 participants per group. Thus, the final target sample size is 100 participants in total (50 per group).

### Randomization and allocation concealment

The participants will be randomized at a 1:1 ratio through a centralized web-based system managed by the Clinical Trial Management Office of Guangdong Provincial Hospital of Traditional Chinese Medicine. A site-stratified block randomization sequence will be generated via SAS (v9.4; SAS Institute Inc.). Allocation concealment will be ensured through centralized drug coding. Center identifiers, randomization numbers, subject identification numbers, and medication codes will be maintained by an independent statistical unit.

### Blinding and emergency unblinding

This was a double-blind trial. The master randomization list and blinding code will be generated and maintained by an independent statistician with restricted access. Investigators, participants, outcome assessors, and site staff will remain blinded until database lock. The study drug and placebo will be identical in appearance, packaging, and labeling. Emergency unblinding will be allowed only when needed for the clinical management of a serious adverse event. Unblinding will be performed through a 24 hour interactive response system and will be documented, including the date, reason, and responsible personnel. It will also be reported to the study monitor within 24 h. Planned unblinding will take place only after completion of the final visit and database lock.

### Intervention and concomitant medication management

#### Study intervention

The participants will receive one of the following treatments:
**STDP group:** guideline-directed standard therapy plus STDP (two pills, three times daily) for 12 weeks;**The placebo group received** guideline-directed standard therapy plus a matched placebo (two pills, three times daily) for 12 weeks.Standard therapy will follow the EAPCI Expert Consensus on the INOCA (16). This treatment may include antianginal drugs, such as beta-blockers, calcium channel blockers, and long-acting nitrates, as well as lipid-lowering therapy, antiplatelet agents when indicated, and risk factor management. Concomitant medications for hypertension, diabetes, or dyslipidemia will be allowed according to clinical needs and must be documented. To reduce confounding, guideline-directed therapies should be kept at stable doses whenever clinically feasible. Any treatment changes and the reasons for these changes will be recorded.

#### Prohibited medications

The use of other Chinese herbal medicines with Qi-tonifying or blood-activating effects will not be allowed during the trial.

#### Compliance monitoring

Adherence will be assessed at each visit via pill counts and participant medication diaries. Electronic monitoring may also be used when feasible. Adherence will be calculated as (doses taken ÷ doses prescribed) × 100%. An adherence rate of at least 80% was considered acceptable. Participants with poor adherence will receive counseling. Persistent nonadherence may lead to the discontinuation of study treatment. Adherence data will be recorded in the eCRF.

### Stress MCE protocol and interpretation

Stress MCE will be performed at baseline via contrast-specific low-mechanical-index imaging (target mechanical index 0.05–0.20) on a standardized platform (EPIQ 7C, Philips Healthcare) with an S5-1 transducer (2.0–5.0 MHz). A sulfur hexafluoride microbubble contrast agent (SonoVue, Bracco Suisse S.A.) will be administered intravenously according to the manufacturer's instructions to achieve homogeneous myocardial opacification. A constant infusion of approximately 1 mL/min will be maintained during rest and stress image acquisition, followed by a saline flush when needed.

Pharmacologic stress will be induced with 0.4 mg of intravenous regadenoson administered over 10 s (*T* = 0). Image acquisition will focus on the hyperaemic window (*T* = 1.5–4 min). Standard apical 4-, 2-, and 3-chamber views will be obtained at rest and during steady-state hyperemia. Destruction–replenishment imaging uses a brief high-mechanical-index flash (approximately 0.8–2.0), followed by replenishment cine recording for at least 10–15 s at a frame rate of at least 25 frames/s to allow curve fitting. The participants will be asked to avoid caffeine or xanthine-containing products for at least 12 h before testing. Continuous electrocardiographic and noninvasive blood pressure monitoring will be performed throughout the procedure.

All image acquisition will be performed by trained echocardiographers blinded to treatment allocation. DICOM data will be archived and transferred to a core laboratory.

#### Qualitative assessment

Two independent expert readers (≥10 years of experience), blinded to the clinical data and treatment allocation, evaluated the perfusion patterns. Disagreements were resolved by consensus or by a third reader. Perfusion abnormalities are classified as perfusion delay, perfusion reduction, or perfusion defects according to core laboratory criteria.

#### Quantitative assessment

Offline analysis will be performed via iMCE software (Narnar, China). The left ventricle was segmented according to the American Heart Association (AHA) 17-segment model. Standardized regions of interest (5 × 5 mm) will be placed within the myocardium, with motion tracking and manual adjustment when needed. The time‒intensity curves were fitted with the following equation:$$y(t)\;=\;A\;\times \;(1\text{-}e^{\wedge \;}(\text{-}\beta t))\;+\;B$$In this model, A represents microvascular blood volume, *β* represents microvascular flow velocity, and A×*β* estimates MBF (17). The CFR is calculated as the ratio of the stress MBF to the remaining MBF at the segmental level. The global CFR is obtained by averaging the segmental values. Interobserver and intraobserver variability will be assessed in a random 10% sample.

### CPET protocol and interpretation

The CPET will be performed at baseline and at week 12 according to the AHA and EACPR/AHA scientific statements (18, 19). A symptom-limited incremental protocol will be used on an upright cycle ergometer (Schiller CS200 ERGO) with breath-by-breath gas analysis (Brilliance/SDS-200), and the data will be averaged over 15 sec intervals.

Participants will be instructed to withhold medications that may substantially affect heart rate or blood pressure, such as beta-blockers, calcium channel blockers, and nitrates, for 24 h before testing when clinically safe. They were also instructed to fast and avoid smoking or caffeine for at least 2 h before the test. The protocol will include 2 min of rest, 3 min of warm-up at 20 W, and then incremental loading starting at 25 W with an increase of 25 W every 2 min until voluntary exhaustion or a termination criterion is reached. This was followed by active recovery at 20 W for 3 min and passive recovery for 3 min. Continuous 12-lead electrocardiographic monitoring will be performed, and blood pressure will be measured every 2 min. A peak respiratory exchange ratio (RER) >1.1 will be used as a criterion supporting maximal effort (19, 20). Tests will be stopped for chest pain, significant ST-segment changes, abnormal blood pressure responses, or serious arrhythmias.

The main CPET parameters will include peak VO₂ (mL/kg/min and % predicted), oxygen pulse, *Δ*VO_2_/*Δ*work rate slope, heart rate reserve, and 1 min heart rate recovery (21). The ventilatory anaerobic threshold will be determined by the V-slope method with manual confirmation (22). All tests will be performed by a trained team via a standardized protocol.

### Outcomes

#### Primary outcomes

The primary outcome will be assessed from baseline to week 12 as the change in peak VO₂ measured by the CPET. This primary endpoint provides a comprehensive assessment of functional capacity, integrating both cardiac and peripheral contributions to exercise limitation, and serves as a well-established prognostic marker in patients with cardiovascular disease.

#### Secondary outcomes

The secondary outcomes will be assessed at baseline and week 12 and will include the following:
**Biomarkers:** lipid profile, homocysteine (HCY), high-sensitivity C-reactive protein (hs-CRP);**CPET parameters:** additional functional indices as described above;**Symptoms and patient-reported outcomes:** Seattle Angina Questionnaire (SAQ) score, Chinese medicine symptom scoring scale, and visual analog scale (VAS);**Psychological status:** Patient Health Questionnaire-9 (PHQ-9) and Generalized Anxiety Disorder-7 (GAD-7);**Quality of life:** EuroQol Five-Dimension scale (EQ-5D).All scale-based assessments will be independently completed by two physicians with at least 5 years of clinical experience, and any disagreements will be resolved by consensus.

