### Follow-up, discontinuation, withdrawal, and data management

Eligible participants will be identified on the basis of stress MCE findings during the screening period, with confirmation of CMVD requiring evidence of reduced myocardial perfusion or perfusion defects. Following enrollment, participants will attend onsite visits at week 0 (baseline), week 8 (±7 days), and week 12 (±7 days). Comprehensive efficacy assessments, including the CPET, laboratory tests and safety evaluations, will be conducted at both the baseline visit and the week 12 visit. The week-8 visit will focus on adherence, review of concomitant medication, symptom and patient-reported outcome assessment, and interim safety monitoring (Table 1). Stress MCE is performed only at screening for diagnostic confirmation and is not repeated during follow-up.

**Table 1 T1:** Schedule of assessments and data collection time points for the hybrid study.

Period	Screening period	Pretreatment	Treatment period	Treatment period	Follow-up period
	−1 week	0 week	8 weeks	12 weeks	16 weeks
Baseline information					
Informed consent	√				
Eligibility screen	√				
Demographics and medical history	√				
Physical examination and vital Signs	√			√	
Randomization					
Diagnostic confirmation					
Stress MCE	√				
Outcome measurements					
CPET	√			√	
Echocardiography (Conventional Parameters) and ECG	√				
Laboratory tests(lipid profile, HCY, hs-CRP)	√			√	
SAQ	√		√	√	
Health questionnaires (PHQ-9, GAD-7)	√			√	
Chinese medicine symptom scoring scale	√			√	
Safety assessments					
Liver function	√			√	
Renal function	√			√	
Adverse events			√	√	√
MACEs			√	√	√
Others					
Concomitant medication record	√	√	√	√	
Evaluate compliance			√	√	

HCY, homocysteine; hs-CRP, high-sensitivity C-reactive protein; SAQ, seattle angina questionnaire; PHQ-9, health questionnaire depression scale; GAD-7, generalized anxiety disorder scale; ECG, electrocardiogram; MCE, myocardial contrast echocardiography; CPET, cardiopulmonary exercise testing; MACEs, major adverse cardiovascular events.

“√” represents the need for implementation at this point in time.

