#### Secondary outcomes

Continuous secondary outcomes—including laboratory parameters, patient-reported outcome scores, and CPET indices other than peak VO_2_—will be analyzed as changes from baseline via ANCOVA with baseline adjustment. If distributional assumptions are violated, rank-based ANCOVA or nonparametric methods (e.g., the Mann–Whitney *U*-test) will be applied. Categorical outcomes will be compared via the chi-square test or Fisher's exact test, as appropriate. Exploratory analyses will assess correlations between changes in peak VO_2_ and improvements in symptoms or quality of life (e.g., SAQ scores) via Pearson or Spearman coefficients. Safety outcomes, including adverse events, major adverse cardiovascular events, and changes in liver and renal function, will be summarized descriptively and compared between groups where applicable.

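### The rule for secondary outcomes has two physicians complete every scale and settle differences by consensus, which contradicts the protocol's own patient-reported label

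*Protocol article*

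**What the plan says.** The Outcomes section of the protocol article (*Secondary outcomes*) names six scales:

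- SAQ, a Chinese medicine symptom scale and a VAS, grouped under "Symptoms and patient-reported outcomes";
- PHQ-9 and GAD-7, under psychological status;
- EQ-5D, under quality of life.

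The list closes with one rule for all of them: "All scale-based assessments will be independently completed by two physicians with at least 5 years of clinical experience", and "any disagreements will be resolved by consensus".

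Elsewhere the article describes such data as coming from the patient:

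- In *Follow-up, discontinuation, withdrawal, and data management*, the week-8 visit includes "review of concomitant medication, symptom and patient-reported outcome assessment, and interim safety monitoring".
- *Data collection and management* lists patient-reported scores among the key variables that receive range and logic checks.
- *Statistical analysis, Secondary outcomes* names "patient-reported outcome scores" among the continuous outcomes for baseline-adjusted ANCOVA. It also plans exploratory correlations of change in peak VO₂ with symptom or quality-of-life improvement, giving SAQ as the example.

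**The concern.** Angina burden, mood, anxiety and health state, as these questionnaires record them, are the patient's own account. Two physicians have nothing to adjudicate about what a patient answers. If each physician fills in the form and the pair then agree on a score, the recorded value is a negotiated rating and the patient's answer is lost.

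What is at stake is the meaning of nearly all the symptom, psychological and quality-of-life evidence. A difference between arms on SAQ would be a difference in physicians' consensus about angina. The planned correlation of peak VO₂ change with SAQ would relate exercise capacity to that consensus. Different physician pairs, across six named hospitals, also bring in rater variance that the patient's own answers would not carry.

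Analysis cannot repair this later: an answer that was not captured at baseline or week 12 cannot be recovered.

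**Working it through.** No arithmetic applies, since the plan states no figure on this point. The check sets the statements side by side.

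1. **Reach of the rule.** It applies to all scale-based assessments and lists no exemption. Nowhere does the article say that the participant supplies the answers to any scale. All six instruments therefore fall under it.

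2. **Where the contradiction is explicit.** The patient-reported heading covers SAQ, VAS and the Chinese medicine scale. For SAQ and VAS, the heading and the rule stand in the same section and cannot both hold. The Chinese medicine scale shares the heading but may well be clinician-rated, in which case it is the heading that is loose.

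3. **Where it is indirect.** PHQ-9, GAD-7 and EQ-5D sit under other headings. The patient-reported wording in the follow-up, data management and statistical sections names no instruments, and SAQ is the only scale that Table 1 marks at week 8. For these three the problem is that they too record the patient's own state, yet come under the physician rule.

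4. **Does the rule merely mean handing out the form?** The physicians work independently and reconcile disagreements. Where the datum is the patient's answer, no disagreement between raters arises. The article uses a similar scheme for reading MCE images (*Qualitative assessment*): two independent readers, with consensus or a third reader. There it fits, because the reading is an expert judgement. Applied to a questionnaire, it treats the score as a judgement too.

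5. **Count.** Six scales, less the Chinese medicine scale, leaves five: SAQ, VAS, PHQ-9, GAD-7 and EQ-5D.

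6. **What is not touched.** The primary endpoint is peak VO₂ from CPET. The sample size, randomization, eligibility and safety rules do not depend on these scales.

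7. **Direction of any effect.** *Blinding and emergency unblinding* keeps investigators, participants and assessors blinded against a matching placebo. Rater expectation should therefore not differ by arm. What remains is lower validity and added rater variance, and nothing in the article allows either to be quantified.

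**The case against.** The strongest reply is that the sentence is loose wording. It may mean interviewer administration, or independent double scoring of answers that the patient gave, where scoring discrepancies can arise. The article is condensed, and it refers to operating procedures and standardized training that are not shown. This reply has some force: actual conduct at the sites cannot be read from the article. It does not remove the point, because the article states a rule and that rule conflicts with its own label. If the intended meaning is different, the sentence still needs correcting.

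A second reply is that the comparison is within the trial, blinded, baseline-adjusted and made with the same procedure in both arms. Randomization is stratified by site, and *Data collection and management* says models will include site as a random effect. Two ratings may even reduce measurement error. This largely stands as far as bias between arms is concerned. It does not restore the meaning of the score: a more precise physician rating is still not the patient's report. A site effect can absorb stable differences between sites, but not differences between physician pairs within a site.

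A reader might infer more than the documents support:

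- *That the treatment comparison on these scales is biased.* Blinding and the matched placebo argue against this, and no mechanism that differs by arm is shown.
- *That consensus shrinks or shifts the scores.* Nothing in the article supports a size or a direction.
- *That the article labels all five questionnaires patient-reported.* The explicit heading covers only SAQ and VAS among them.
- *That the scores already collected are physician opinions.* The article shows what is instructed, not what was done.

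**Conclusion.** The point holds as an internal contradiction in a stated rule, and it should be fixed. It concerns secondary outcomes only. The contradiction is explicit for SAQ and VAS. For PHQ-9, GAD-7 and EQ-5D it follows from the nature of the instruments. If the rule is followed as written, five of six scales become physician-consensus ratings, and the symptom, psychological and quality-of-life results and the exploratory SAQ correlation lose validity and interpretability.

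The primary endpoint and its analysis are unaffected. The harm is to validity, with some added rater variance; bias between arms is not demonstrated, and no numerical size can be given.

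The conclusion assumes that sites follow the sentence as printed and that no unseen procedure overrides it. Exempting the Chinese medicine scale assumes that it is clinician-rated, which the article does not say.

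**What to change.** Replace the closing sentence of *Secondary outcomes* with a rule along these lines: *The participant supplies the answers to SAQ, VAS, PHQ-9, GAD-7 and EQ-5D, either by self-completion or, where help is needed, with the items read aloud and the answers recorded verbatim. The mode is kept the same at each visit. Staff check completeness and scoring only. Rating by two physicians with consensus applies to the Chinese medicine symptom scale.* The last sentence should stand only if that scale is in fact clinician-rated.

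Self-completion alone, before any contact with a clinician, is not required to remove the contradiction; assisted recording of the patient's own answers also does so.

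For participants already enrolled, record how each scale was completed, so that physician-rated values can be identified. The article reports one participant as of June 12, 2025, and recruitment planned to the end of 2027. The present count is not given, but the earlier the change, the fewer participants are affected.

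The cost is a one-sentence amendment, with ethics approval and an instruction to sites. It saves the time of two physicians per assessment on the five questionnaires. The small downside is that some participants will need help with reading.
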